| SAMPLING  Study sampling and sample sizes:  Our study sampling frame will consist of all (approximately 35) studies being tested in the Reproducibility Project:Cancer Biology. We will categorize the studies based on theoretical and practical features. We will remove studies due to lack of feasibility (e.g. if there is not a clear relevant effect to predict, such as many in vitro studies especially those focused on cell signaling; if maturation date is too far in the future). We will prioritize studies whose results will be published sooner.  We will work with an independent expert to create or edit two to three questions for each study that can be rendered into dichotomized forecasts. In stage 1, participants will forecast all of the first six (all based on mouse models) studies from the cancer reproducibility project plans to publish. Participants will answer two binary elicitations for six events and simplified continuous elicitations for two events.  When mouse survival or tumor growth curves are used, questions will be created around them. When there are no mouse studies, we will shape a question around a study with a quantitative outcome. We plan to conduct a brief pilot to ensure the question types are relatively intuitive. Question formats might vary slightly depending on pilot results.  For the binary elicitation, our questions will take the two^[[2]](#footnote-2)^ of the following general forms:   1. How likely is it that the replication also be significant (at p ≤ .05)? 2. How likely is it that the effect size of the replication will be as large or larger than the original effect size?   For the simplified continuous elicitation (SCE) for the effect size of the specified treatment group, we will use a four question format, based on [9]:  1. What is the lowest effect size you realistically anticipate will be reported for study X?  2. What is the highest effect size you realistically anticipate will be reported for study X?  3. What is your best guess of the effect size you realistically anticipate will be reported for study X?  4. How confident are you (from 0% to 100%) that your estimated interval (lowest to highest) will include the reported effect size from study X?  Investigator sampling and planned strata:  All respondents will be at least 18 years old and will complete an informed consent.  Our primary sample will include two strata:  *a) Independent Experts*: we will create a sample of about 50 to 100 eligible independent international experts by compiling a list of authors from two searchers based on each original study undergoing replication: a) *related article* searches on PubMed and b) articles citing the original report. We will include corresponding authors and anyone who appears at least three times in any single search.  b) Novices: we will recruit a sample of about 50 to 100 medical undergraduate or upper level undergraduate biology majors, graduate students, or postdoctoral fellows at various universities via department mailing lists to participate in our study.  We will aim to include two secondary strata^[[3]](#footnote-3)^:  *c) Originators*: we will contact each co-author on each original research publication for an elicitation.  *d) Replicators*: we will contact each co-author on each replication protocol - only in cases where data collection has not yet been initiated.  Subjects will be approached through email (except non-experts, who may be approached in a class), and administered the questionnaire electronically.  Individuals will be approached up to five times before declaring them as having declined participation.  Sample size:  Our target sample size is as follows:  We will collect forecasts on 3 events in a half hour. We will collect 2 binary forecasts on 6 effects from 6 experiments + simplified continuous forecasts on overall replication rates). We will split the trial sample into two surveys to minimize the number of trials for which participants only have general expertise.  We will target 30 forecasts per participant on 6 events.  We will aim for 150 participants (50X2=100 independent experts + 50 novices) and expect a minimum of 90 (30X2=60 independent experts + 30 novices). |

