| INTERVIEW AND DATA COLLECTION  Interviews will be conducted in 2 stages:   1. Intake interview: in one 30-minute survey presented over the internet (or in person, or by paper and pencil), we will present subjects with a one-page summary sheet describing each replication study (see Appendix 2), as well as a questionnaire (see Appendix 3). Individuals will be approached using appropriate elicitation technique, whereby we first a) describe the goals of the project and how to complete the questionnaire; b) attempt to motivate good performance by explaining how scoring works; c) provide a simple warm up question (asking for a weather forecast); d) elicit replication forecasts; and e) collect additional cognitive and attitudinal measures. The questionnaire will first collect forecasts, then individual difference variables (as applicable), then demographic variables. 2. Forecasts: subjective probabilities on target experiments.    - 1. 2 binary: Significant difference and direction on 3 replication studies      2. 2 @ 4 parameter simplified continuous (best estimate, range, confidence) on overall replication rates.    1. Individual difference variables       1. Actively Open-Minded Thinking[10]       2. Pace of progress of medical research (AKA Medical Boomster-Doomster, adapted from [11])       3. Self-report of expertise for each study       4. Confidence rating of each forecast       5. Time for forecasts       6. Evidence reliance       7. Familiarity with and Anticipated Impact of Reproducibility Project       8. Estimate of perfect replication of effect sizes    2. Demographics:       1. age       2. gender       3. expertise: H index, title/rank (associate professor, full professor, etc.), number of publications, number of citations (all collected from both SCOPUS & Web of Science), nationality/region 3. Post-event Interview: Once results are available, all participants will be approached for posterior and recalled forecasts. We will collect the first set of posterior distributions when the first batch of results is published. Once all data are collected, we participants will be debriefed about study hypotheses and offered an opportunity to learn their forecast skill against the average of their peers. |

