| PRIMARY ANALYSIS  We will calculate the Brier scores of each individual forecaster, and present a distribution. A Brier score is a proper scoring rule – meaning it incentivizes honest reporting of subjective beliefs – which measures the accuracy of a forecast: BS = 1/N $\sum_{i=1}^{N} \left( f_{i}-o_{i} \right)^{2}$ where *f_i_* is a forecast and *o_i_* is a realized outcome for each of i events.[12] We will decompose into calibration = 1/N $\sum_{i=1}^{N} {1/n_{i}\left( f_{i}-\bar{o}_{i} \right)}^{2}$, and discrimination = 1/N $\sum_{i=1}^{N} 1/n_{i}(\bar{o}_{i}\left( 1-\bar{o}_{i} \right))$.[13] We will construct calibration curves for individual forecasters. Our null hypothesis is that mean Brier score 95% confidence intervals exclude Brier score for a matched sample size of hypothetical forecasters predicting same trials using a random number generator. We will also measure the Brier Skill Score for individuals: BSS = 1 – BS/BS_ref_ where BS_ref_ is the base rate for the reference class or of a confidence interval. The sample variance can be used when is BS_ref_ unknown.[14]  Primary endpoint   1. Replicability rate measures: The brier scores for aggregate measures will be slightly higher than .25 (note: .25 is the equivalent of a 50-50 prediction meaning “I don’t know” or a random guess). The mean forecaster will perform slightly worse than base-rates. Forecasts will be skewed toward predicting more successful replications than observed, but less than statistically expected. The order of successful predictions of aggregate replicability rates will be: 2. Effect sizes at least as large (Brier of about .20 to .25) 3. Significance (p-values) (Brier of about .25)   An a priori power analysis suggests we need a sample size of 34 to detect if expert Brier scores are different than a constant (e.g. random guessing (BS = .25) or a base rate (e.g. 80% of significant effects in cancer phase 3 trials favor the new treatment[15]) by a moderate degree (difference from a constant of Cohen’s d = .5) assuming power = .80 and alpha = .05.   1. Individual study measures: The Brier scores for individual studies will be slightly lower than .25. Forecasts will predict more successful replications than observed. Brier scores will be lower (forecasts will be more successful) for forecasting the direction of the difference between effect sizes (Outcome2) compared to forecasting significant differences (Outcome1). Base-rates will outperform the typical forecaster, but aggregating the top-tier of forecasters will beat base-rates. |

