| SECONDARY ANALYSIS ON FORECAST SKILL^[[4]](#footnote-4)^  An a priori power analysis suggests we need a sample size of 34 per group to detect if detect if the experts differ from (d = .5) the novice group assuming power = .80 and alpha = .05, and we need about 180 total respondents to detect a moderate difference (f = .25) between all four strata. As analysis is exploratory, we do not intend to correct for multiple hypothesis testing.   1. Expert strata analysis: 2. The order of predicted replication rates will be: 3. Novices/Non-experts (Should be optimistic since and less attuned to the “replicability crisis” across scientific disciplines) 4. Originators (if available- should be optimistic due to their investment in these results, but more realistic than novices) 5. Independent Experts (Should be less biased due to independence from findings) 6. Replicators (if available- theoretically well attuned to flawed research design and practices) 7. The order of forecast skill will be: 8. Independent Experts (should have sufficient expertise and less biased by own work) 9. Originators (if available- should have sufficient expertise, but more myside bias) 10. Replicators (if available- assumes lab skills are higher than knowledge for this group) 11. Novices/Non-experts (assuming expertise and forecast skill are related, they have the least expertise) 12. The order of variability in forecasts will be: 13. Novices/Non-experts (assuming expertise and forecast skill are related, there should be more variability for those with the least knowledge) 14. Independent Experts 15. Replicators (if available- assumes replicators are well attuned to good and bad study design and difficulty of carrying out certain studies) 16. Originators (if available- assuming expertise and forecast skill are related, there should be less variability in recognizing real empirical relationships and flawed study design by those who have devoted their lives to studying these topics) 17. Expertise will have an inverse U-shaped (∩) relationship with forecasting success. People with low expertise will perform poorly due to inadequate information, and people with high expertise will perform poorly due to maladaptive beliefs (e.g. confirmation bias). The correlation between perceived expertise and Brier score will be ranked as follows:      1. Originators (if available- should perform when they claim higher expertise; have motivation to honestly claim high expertise for some, but not all topics) 2. Independent Experts (may be less discriminating in expertise ratings than originators since they don’t have personal relationships with any of the studies) 3. Replicators (if available) 4. Novices/Non-experts (should have consistently low expertise ratings) 5. Predictors of Forecast Skill: We will test the relationship between each demographic and scale variables and Brier Skill Score, secondarily looking at components of calibration and discrimination. The individual differences should influence the forecasts in the following order (from most to least influential). 6. More extreme updaters: Those who update more extremely relative their will have more accurate forecasts^[[5]](#footnote-5)^. 7. Pace of progress: Those who believe medical technology should progress quickly (slowly) will have more optimistic (pessimistic) forecasts. 8. Evidence reliance: 9. Those who rate the methodology of the replication attempt as important will be pessimistic. 10. Those who cite specific trial outcomes as evidence will be worse forecasters, and those who cite treatment or disease type (base rates) will be better forecasters. 11. Expertise: Those will high (self-reported and actual) expertise will be more accurate; actual expertise (H- & M-indices) will be more predictive of forecasting skill. 12. Confidence will be weakly correlated with forecasting skill. We expect a hard-easy effect where forecasters are overconfident on hard items and underconfident on easy items. 13. Demographics     1. We will also test methods of identifying forecasting skill early (prior to target event realization) the relationship between individual forecaster’s Brier scores and their average squared distance to the median compared to other baselines (mean, expectation due to chance, expectation due to base rates if available) - we hypothesize that this will lead to a strong relationship with forecast skill. 14. Aggregation of Forecasts 1: We will test whether different aggregation approaches give better forecast performance (i.e. lower Brier scores). First, to determine the relative value of using combined forecasts to make decisions, we will construct a curve of showing the relationship between Brier scores and number of aggregated forecasts. Specifically, the curve will reflect n=0 aggregation (i.e. average Brier scores of individual forecasters); n=1 (i.e. average Brier score when two forecasters forecasts are randomly aggregated); n=4 (i.e. average Brier score when 5 randomly selected forecasts are aggregated); and n=9 (i.e. average Brier score when 10 randomly selected forecasts are aggregated). We will also use transformations to make predictions more extreme.[16,17] 15. Predictors and Aggregation: Using individual differences and demographic variables that show low skill identified in step 1, we will test the competitiveness of aggregated low skill forecasters with the individual scores of high skill forecasters. For instance, suppose we find a relationship between high M-index and high forecast skill. We will then test whether, if we combine forecasts from 2, 3, 5 and 10 low M-index forecasters, on average the forecast outperforms the average forecast of high M-index forecasters.   After we have completed forecast scoring, we will also rank all individual forecasters by their Brier skill scores, and randomly select individuals within tiers of upper, middle, and lower thirds. We will test whether combined forecasts of 2, 3, 5 and 10 “low skill” forecasters can, on average, beat the forecast of randomly selected individuals from each skill tier. Brier scores will be used; as well, they will be decomposed into discrimination and calibration. |

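### The printed calibration and discrimination formulas do not decompose the Brier score, and six binary forecasts per person are too few for individual components or calibration curves

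*Protocol*

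**What the plan says.** All references are to the protocol.

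- **Primary Analysis** defines the Brier score as the mean of (f_i − o_i)², where o_i "is a realized outcome for each of i events". It continues "We will decompose into calibration = 1/N" times the sum over i = 1 to N of (1/n_i)(f_i − ō_i)², "and discrimination = 1/N" times the sum of (1/n_i) ō_i(1 − ō_i). Neither n_i nor ō_i is defined. The same section gives .25 as the score of a 50-50 forecast and promises: "We will construct calibration curves for individual forecasters".
- **Secondary Analysis on Forecast Skill** relates forecaster traits to the Brier skill score, "secondarily looking at components of calibration and discrimination", and decomposes scores again in the skill-tier comparisons. The section on updating and recall repeats all primary and secondary analyses.
- **Interview and Data Collection** sets each person's binary task: "2 binary: Significant difference and direction on 3 replication studies". Every survey version in the Protocol Appendix lists three studies.
- **Sampling** has participants forecasting all of the first six studies, but also mentions three events in half an hour, a split into two surveys, and: "We will target 30 forecasts per participant on 6 events".
- **Footnote 4** says that some of the forecast-skill analyses could not be done, partly because the replication results varied too little. It does not name the decomposition.

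**The concern.** A decomposition is useful only if its parts rebuild the score and each part means what its name says. Here the weighting looks inverted, and the term called discrimination falls as forecasts separate successes from failures better. An analyst who codes the formulas as printed gets wrong components for any tied, binned or pooled data. A reader who takes higher discrimination as better reverses the direction of any association with a forecaster trait.

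The second issue is sparsity. Calibration compares a stated probability with the observed frequency among forecasts at that probability. With six forecasts there is little or nothing to average within a level. The individual curves and the component-level predictor analyses would then describe chance rather than skill.

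**Working it through.** **Inputs.** The formulas and the .25 benchmark come from Primary Analysis. The binary forecasts per person come from Interview and Data Collection and the survey versions: 2 questions × 3 studies = 6.

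**1. The identity.** Let k index the distinct forecast values, n_k the forecasts at value f_k, and ō_k their observed success proportion. For binary outcomes, the mean of (f_k − o)² within level k equals (f_k − ō_k)² + ō_k(1 − ō_k). Averaging over all N forecasts gives

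BS = (1/N) Σ n_k(f_k − ō_k)² + (1/N) Σ n_k ō_k(1 − ō_k).

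So n_k multiplies. If the sum runs over events, each level is already counted n_k times and no factor is needed. The printed 1/n_i is wrong under both readings.

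**2. The plan's own benchmark.** Take six forecasts of .5 with three successes.
- Brier score: 6 × .25 / 6 = .25, as the protocol states.
- Correct weights: 0 + (6 × .25)/6 = .25.
- Printed, i = event: 0 + (1/6) × 6 × (.25/6) = .0417.
- Printed, i = bin and N = forecasts: 0 + (1/6) × (.25/6) = .0069.

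**3. A second example.** Forecasts .8, .8, .8, .4, .4, .4 with outcomes 1, 1, 0, 0, 0, 1.
- Brier score: (.04 + .04 + .64 + .16 + .16 + .36)/6 = .2333.
- Correct weights: .0111 + .2222 = .2333.
- Printed: .0037 + .0741 = .0778 (event), or .0012 + .0247 = .0259 (bin). If the square also covers 1/n_i, the bin reading gives .0251.

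**4. Direction of the second term (correct weights).**
- Forecasts .9 ×3 and .1 ×3 that separate outcomes perfectly: 0.
- Forecasts .9, .9, .1, .1, .5, .5 with outcomes 1, 0, 1, 0, 1, 0, which separate nothing: .25.

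The term is therefore refinement. Discrimination in the usual direction is the between-bin term (1/N) Σ n_k(ō_k − ō)², and it needs the uncertainty term ō(1 − ō) to close the sum. In step 3: .0111 − .0278 + .25 = .2333.

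**5. Six forecasts per person.**
- *All distinct* (.9, .75, .6, .5, .4, .2; outcomes 1, 0, 1, 0, 0, 0): every n_k = 1 and every ō_k is 0 or 1. Calibration = Brier = .1971 and the plan's discrimination = 0, with or without the 1/n_i error. The between-bin term does no better: it equals the uncertainty (.2222) whatever the forecasts are.
- *All outcomes agree* (.8, .8, .6, .6, .4, .4; no successes), correct weights: calibration = Brier = .3867, and every other term is 0.
- *Otherwise:* a forecaster was simulated whose outcomes occur with exactly the stated probability, so true calibration error is 0. There were 4,000 runs with correct weights; uniform forecasts are an assumption.

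| Forecasts | Response scale | Mean calibration term | Runs with refinement exactly 0 |
| --- | --- | --- | --- |
| 6 | all distinct | .166 | 100% |
| 6 | 11 points | .127 | 64% |
| 6 | 5 bins | .103 | 42% |
| 6 | 3 bins | .079 | 27% |
| 12 | 11 points | .096 | 17% |
| 30 | 11 points | .053 | 0% |

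At six forecasts the standard deviation of the calibration term is .063 to .080, as large as many of the differences one would hope to detect.

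**6. What is unaffected.** The Brier formula contains no n_i. A two-sided one-sample t-test with n = 34, d = .5 and alpha = .05 has power .808, so the stated 34 reproduces and does not depend on the decomposition.

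**The case against.** A fair defence has five parts.

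- *The two faults hardly overlap.* For a person with distinct forecasts n_i = 1, so the printed factor does no harm and the parts do sum to the Brier score. This stands. The weighting error matters for ties, bins and pooled data. A typesetting slip is possible, but the same factor stands in both terms, so one stray character is an unlikely explanation.
- *Refinement is a legitimate second term.* This also stands. All respondents to one survey version face the same outcomes, so their uncertainty is constant and correctly weighted refinement ranks them exactly opposite to between-bin discrimination. The fault is the name and the missing statement of direction.
- *The individual components are not always empty.* A reader might infer that they never carry information. The protocol does not support that: it does not exclude rounding or binning, and in the simulation refinement was non-zero in 36%, 58% and 73% of runs on the 11-point, 5-bin and 3-bin scales. They remain too biased and noisy to interpret.
- *The components are secondary.* The predictor and tier analyses are declared exploratory, and tiers are ranked by Brier skill score. This limits the damage but does not make the formulas right.
- *Thirty may not mean thirty per person.* Sampling gives its minimum as 30 × 2 = 60 experts, so 30 could be forecasters per survey. The text needs reconciling; nothing shows that 30 should simply become 6.

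**Conclusion.** The point holds in two separate parts.

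1. **Formulas.** They are wrong under every reading tried once a forecast value repeats. On the plan's own benchmark the components recover .0417 or .0069 of .25. The second term is mislabelled, and its direction is opposite to its name. How far pooled results would be off depends on the reading and the data, so no single figure for the trial can be given.
2. **Sparsity.** With six binary forecasts per person, individual components are exactly degenerate when forecasts are distinct or outcomes agree. Otherwise they are strongly biased: a perfectly calibrated forecaster shows a mean calibration term of .079 to .127 on the scales tried, where 0 is the truth. The exact statements are algebra; the bias figures rest on the uniform-forecast assumption. Individual calibration curves and component-level predictor analyses are therefore not interpretable.

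A reader might infer that the primary result is compromised. It is not: the comparison of mean Brier scores and the calculation behind n = 34 do not use the decomposition. Nor does footnote 4 dispose of the matter, since it neither corrects the formulas nor withdraws the individual curves.

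**What to change.** 1. **State the decomposition correctly,** defining k, n_k and ō_k: BS = (1/N) Σ n_k(f_k − ō_k)² − (1/N) Σ n_k(ō_k − ō)² + ō(1 − ō), with the middle term as discrimination (higher is better). Alternatively keep two parts with n_k as multiplier, call the second refinement, and state that lower is better. If forecasts are grouped into bins, say what value represents each bin; the identity is exact only when all forecasts in a bin share that value.
2. **Report components and calibration curves only for pooled forecasts, as description.** Pooling adds forecasters, not outcomes: six study outcomes per question underlie the expert results, and three the novice results (only one novice survey is listed). If those outcomes agree, the components collapse again.
3. **For individuals,** drop the curves and components. Report the Brier score and signed bias, that is, mean forecast minus mean outcome.
4. **Reconcile the counts.** Sampling (all six studies; three events; 30 forecasts per participant on six events) must agree with the three studies and six binary forecasts in Interview and Data Collection and the survey versions. The authors should say what the 30 refers to.

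The cost is a text correction and the loss of individual outputs that the data could not support. Data collection, sample size and the primary comparison stay as they are.

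### The primary null hypothesis is stated backwards, and chance is defined both as a random-number score and as .25, which cannot be the same benchmark

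*Protocol*

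**What the plan says.** Everything at issue stands in the protocol's PRIMARY ANALYSIS section.

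- **The test.** "Our null hypothesis is that mean Brier score 95% confidence intervals exclude Brier score for a matched sample size of hypothetical forecasters". The comparator is "hypothetical forecasters predicting same trials using a random number generator". The generator's distribution is not given.
- **The endpoint note.** "note: .25 is the equivalent of a 50-50 prediction meaning “I don’t know” or a random guess". The text below it then predicts results relative to .25: slightly above it for aggregate replicability rates, slightly below it for individual studies.
- **The power statement.** "An a priori power analysis suggests we need a sample size of 34 to detect if expert Brier scores are different than a constant". One of its two examples of such a constant is "random guessing (BS = .25"; the other is a base rate. The effect size is d = .5, with power .80 and alpha .05.

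The section also plans a Brier skill score against a reference, and comparisons with base rates.

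**The concern.** There are two faults in the one sentence that defines the primary test.

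First, the direction. A null hypothesis states the benchmark value, and an interval that excludes that value is the reason to reject it. The sentence makes the exclusion itself the null, so read literally, a clear difference from random would support the null.

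Second, the comparator. Lower Brier scores are better, so the level set for chance decides what counts as better than chance. The section gives chance as the score of random-number forecasters in one place and as .25 in two others, and nothing says which one decides. If the two differ, a panel scoring between them is better than random under one sentence and worse than a random guess under another. The panel most likely to land there is one with no information that stays near 50%.

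**Working it through.** **1. The plan's own figure.** One-sample t-test, two-sided alpha .05, d = .5, n = 34: 33 degrees of freedom, noncentrality .5 × √34 = 2.92, power 80.8%. This is the smallest n that reaches 80%, so the stated 34 reproduces. The calculation is in standardized units, so n does not depend on which constant is used.

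**2. Expected score of a random forecaster.** For a forecast F made without knowledge of the outcome o (0 or 1),

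E[(F − o)²] = Var(F) + (E[F] − o)².

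If F is centred on .5, the second term is .25 for either outcome, so the score is .25 + Var(F):

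| Forecaster | Var(F) | Expected Brier score |
|---|---|---|
| Always 50% | 0 | .25 |
| Uniform on 0–1 | 1/12 = .083 | .333 |
| Random 0 or 1 | .25 | .50 |

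Simulating the uniform case gave .3333 for o = 0 and for o = 1; integer percentages 0–100 give .335. A generator centred on .5 reaches .25 only if it never varies, and then it is not a random number generator.

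**3. Can sampling noise in the simulated comparators close the gap?** For a uniform generator the squared error has variance 1/5 − 1/9 = 4/45. With 34 simulated forecasters:

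- six forecasts each: SD √(4/45/6) = .122, standard error .122/√34 = .0209, 95% range .333 ± .041 = .292 to .374;
- three forecasts each: SD .172, standard error .0295, 95% range .275 to .391.

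Both ranges exclude .25.

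**4. Effect on the conclusion, by formula.** The gap is 1/3 − 1/4 = .083. For 34 experts whose true mean score is .25, the probability of differing significantly from 1/3 depends on the SD of individual scores, which is assumed here:

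| SD of individual scores | Gap as d | Probability |
|---|---|---|
| .10 | .83 | 99.7% |
| .15 | .56 | 88% |
| .20 | .42 | 66% |

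A panel with a true mean of .30, worse than always answering 50%, would still differ from 1/3 in 47% of cases at SD .10 and 16% at SD .20.

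**5. Effect on the conclusion, by simulation.** Inputs: 60 experts (the expected minimum under SAMPLING), forecasts centred on 50% and unrelated to the outcomes, replication probability .3 to .7, and a fixed uniform benchmark of 1/3. INTERVIEW AND DATA COLLECTION gives two binary outcomes on three studies, which is six forecasts per person; three corresponds to scoring one outcome alone. The share of runs with the 95% interval wholly below 1/3 is:

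| Forecast SD (assumed) | Three forecasts | Six forecasts |
|---|---|---|
| 10–15 points | about 100% | about 100% |
| 20 points | 79–81% | 97–98% |
| 25 points | 29–30% | 48–49% |
| 30 points | about 7% | not tabulated |

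The interval lies wholly below .25 in 0% of runs. At 20 points it lies wholly above .25 in 72–73% of runs (three forecasts) or about 96% (six). This agrees with step 2: the expected score is .25 + .20² = .29, between the two benchmarks.

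**6. The plan's own predictions.** Scores slightly above and slightly below .25 both fall under 1/3. A test against a uniform random-number score cannot separate the two outcomes that the section itself distinguishes.

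**The case against.** The strongest reply is that the plan does not rest on this sentence alone. It defines a Brier skill score tied to a base rate, uses it in the secondary analysis to study predictors of skill and to rank forecasters, and tells the reader that .25 means not knowing. A panel hedging at 50% would show up at .25. This stands as mitigation. A reader might infer that hedging would be formally credited as skill; the protocol never says that excluding the random score demonstrates skill, so that reading is not supported. What the sentence would do is declare such a panel different from, and better than, random.

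Three further readings go too far:

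- *The benchmark is 1/3.* Only for a uniform generator, which the protocol does not specify. The conflict with .25 needs less: a generator that varies and is centred on .5.
- *The power analysis is wrong.* It is not. The 34 reproduces and holds for any constant, and .25 is offered there as one example. Only the comparator named differs from the one in the written test.
- *Simulating the comparator is a separate defect.* It adds avoidable noise to a quantity with a known expectation, but that is minor.

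It is also fair that the simulated rate varies steeply with the assumed spread, so no single percentage should be quoted as the size of the problem.

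None of this repairs the reversed null or says which benchmark decides. The protocol states this rule itself, so it is not detail left to an analysis plan.

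**Conclusion.** The point holds in two parts. The reversed null is an error of statement and needs no assumption. The inconsistent benchmark follows from the variance identity for any varying generator centred on .5.

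The size depends on two things the protocol does not give: the generator's distribution and the spread of expert forecasts. With a uniform generator the gap is .083. An uninformed panel near 50% would then usually be called better than random for spreads up to about 20 points, in a minority of cases at 25 points and rarely at 30. Against .25 it would not be. Since the choice of benchmark can reverse the primary reading on the same data, the sentence must be corrected. The sample size needs no change.

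**What to change.** Replace the null-hypothesis sentence with:

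> *H0: mean expert Brier score = .25 (the score of answering 50% to every item). H0 is rejected if the 95% confidence interval excludes .25. Performance better than an uninformed 50% forecast is claimed only if the interval lies wholly below .25.*

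Keep the planned base-rate and Brier skill score comparisons alongside it. With few shared outcomes, a panel that cannot discriminate but leans the same way can also beat .25. In simulations with mean forecasts of 65–80%, SD 20 points and three studies, the interval fell below .25 in about 9–13% of runs at a replication probability of .5 and 35–43% at .7.

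If the random-number comparator is kept, show it as descriptive only, state its distribution and expected score (1/3 if uniform), and do not describe .25 as its score. The endpoint note and the power statement should then call .25 the score of a constant 50% forecast.

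The cost is a few sentences, with no new data and no change to the sample size. The downside is that .25 is harder to beat than a random-number score.
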